## Methods:

**Research Design.** This RCT employs 3 sites (Vancouver, Winnipeg, Quebec City) comparing a 4-week MWC training intervention and wait-list control group among individuals transitioning to MWC use. TEAM Wheels will be delivered in the community specifically targeting new users, defined in the literature as individuals within one year of receiving their MWC.

**Methods.** Participants will be randomly assigned to the TEAM Wheels or control group using a 1:1 allocation ratio between groups. To support balance between groups and masking of assignment, our statistician ([name]. – Quebec City) will create a computerized randomization process with undisclosed block size. Randomization will be stratified by site to ensure comparable treatment group size ( $n \sim 18$  per site). Given the potential benefits of the intervention already reported in our previous studies, control group participants will also receive the TEAM Wheels intervention following a 4-week control period and post-treatment data collection (they will be on a “wait-list” for the TEAM Wheels program and receive **no intervention** during the study period).

Following enrolment, baseline data will be collected and entered into a secure MS Teams database. MS Teams data storage is approved by the University of Manitoba Health Research Ethics Board (HREB) and is *Personal Health Information Act* (PHIA)/*Freedom of Information and Protection of Privacy Act* (FIPPA) compliant. The site Research Assistant (RA) will then obtain the participant’s group assignment and coordinate timing for the first teleconference peer trainer session conducted via the computer tablet; for treatment group assignments this will occur as soon as is practical and for control group assignments this will be scheduled after blinded post-treatment data collection is complete. The Research Assistant will also arrange blinded follow-up (retention) data collection for treatment group participants 6 months after post-treatment data collection. Although collecting 6-month retention data for the control group would be optimal, delaying a potentially beneficial intervention and the associated risk of participant attrition make this option undesirable.

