Data collection for all time periods (baseline, post-treatment, and 6-month follow-up) will be completed by the RA and entered using a laptop computer (into MS Teams). Participant confidentiality will be protected in the following manner: (1) the laptop will be encrypted and

[figure not shown]

password protected. Only the RA using the laptop/tablet will have the passwords and the laptop will be locked in their office in a locked cabinet when not in use, (2) Each participant will be assigned a unique study identification number (Study ID). A separate Master List will be created that contains only the participant's name and study ID number (saved as password protected file on internal research drive); (3) All data entered will be de-identified and coded using only the unique Study Identification Number assigned to each participant, and (4) The data will be uploaded from the laptop to the MS Teams secure storage platform (in de-identified form).

Each of the three study sites (Vancouver, Winnipeg, and Quebec City) will be recruiting and collecting data for n=18 participants (for a total of N=54). The data from each sub-group will be combined for data analysis. Hence, a tri-group data sharing agreement (DSA) will be outlined in the Informed Consent Form (ICF) and implemented; it will include the University information and Principle Investigator of each provincial team lead. De-identified data from each site's sub-group data set will be amalgamated/combined to form the complete data set for analysis. No personal (health) information will be shared across/among research teams. In addition, the fact that the scientific community, the granting agencies, and medical scientific journals are increasingly requiring that data be stored and made available for secondary review and analyses will be outlined in the ICF emphasizing that any information sent out of the University of Manitoba will not show participant's name or address, or any other identifiable personal information about them.

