***eHealth* Home Training Program: Mounting system for in-chair use and software**

The tablet displays feedback to the participant on training activity and weekly progress relative to these targets. The tablet software incorporates over 200 video-based training elements including instruction, peer demonstration, and practice activities and games. The tablet software records all home training activity and uploads this data to a secure server. For participants without Internet access, a portable Wi-Fi hotspot device is provided. The peer trainer monitors participant progress online and may adapt the program, or follow-up with the participant, based on their progress data. Participants and peer trainers can also exchange messages when necessary, using the *eHealth* tablet (participant) and The Zoom/MS Teams platforms or email.

**Control Group.** The control group receives no specific intervention over the course of the 4-week period; this reflects “usual practice” or the typical experience of a MWC user in their provincial context. Participants are placed on a wait-list and receive the TEAM Wheels program, as described, following completion of the study (i.e. after post-treatment data collection from the Intervention group). The site Research Assistant will make contact with control group participants at the end of weeks 2 and 4 during the study period to deter attrition/drop-out. When contact is made at week 4, the Research Assistant will schedule an appointment for post-treatment data collection (week 7). Any formal MWC training received during the wait-list period will be documented for potential post-hoc analysis as a confounding variable; however, research evidence and the investigators’ clinical experience confirm that in all 3 provinces formal training is not provided once MWC users are discharged from hospital.

**Data Analysis.** After testing for assumptions and outliers, between-groups (intervention vs control) comparison of change over time will be conducted using Generalized Linear Modeling (GLM) for participation; MWC skill capacity and performance; self-efficacy; health-related quality of life; and objective MWC mobility parameters ( $\alpha = 0.05$ ). Variables previously identified in the literature as relevant covariates (i.e. age and function as measured by baseline WST-C) will be controlled for. Model fit ( $R^2$ ), regression coefficients ( $CI_{95\%}$ ), and effect sizes ( $F^2$ )

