will be assessed with Maximum Likelihood methods. Data will initially be disaggregated by sex and gender; if analyses prove non-significant, the data will be reaggregated. A repeated-measures ANOVA will be used to evaluate retention of outcomes at follow-up for treatment group participants. Additional post-hoc sub-analyses will investigate the impact of site (using 2-way ANOVA) and length of MWC use covariate (using ANCOVA), although the study is powered only for the primary analysis. Descriptive data will report on recruitment by sex, relative to prevalence data for MWC use to inform generalizability of findings and health services equity balance.

**Sample Size.** The combined results of our feasibility studies found a large effect size ( $f = 0.47$ ) for the WhOM and correlation between measures ( $R^2$ ) was 0.63. Using a comparable effect size ( $f = 0.45$ ) and measure correlation (0.6),  $\alpha = 0.05$ , and 90% power for a between-factors ANOVA repeated measures design, a sample size of 42 is required (G\*Power v.3.1.9.2). Adjusting for 20% loss to attrition, a total sample size of 54 was determined (i.e. 27 per group; intervention and control). We anticipate recruiting 1-2 participants/per site/per month, estimating 12 months required to recruit the sample. Incorporating the treatment and 6-month follow-up periods, the maximum data collection period should be 19 months. While we have built in a 20% attrition rate, our feasibility studies reported 5-10% drop-out rates, (Best et al., 2017; Giesbrecht & Miller, 2017) and with the provision of the TEAM Wheels program to control group participants after data collection, we anticipate little attrition.

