### **Study Sites.**

The three study sites offer varied provincial approaches to MWC procurement as well as differences in geography, culture and climate, and provincial COVID-19 recommendations and guidelines (Phase of restrictions) to prevent infection. This diversity allows TEAM Wheels delivery in multiple contexts; site-specific post-hoc analyses may provide additional insights. Sites are major urban centres with access to a large number of MWC users. In Manitoba, approximately 1800 MWCs were distributed to first-time users in 2016, primarily within Winnipeg (pop ~700,000). The population of Quebec City is comparable and Vancouver is over three times as large, providing a sizable pool of potential participants.

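### Randomisation is stratified by site but the between-group model omits site; if site predicts change, standard errors will be somewhat too wide and the test conservative.

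*Protocol*

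**What the plan says.** In the Protocol, under Methods, participants are allocated "using a 1:1 allocation ratio between groups" in blocks of undisclosed size, and "Randomization will be stratified by site to ensure comparable treatment group size". The same section sets the site target: "Each of the three study sites (Vancouver, Winnipeg, and Quebec City) will be recruiting and collecting data for n=18 participants". The three data sets are then pooled for analysis.

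The Data Analysis paragraph says that a between-group "comparison of change over time will be conducted using Generalized Linear Modeling (GLM) for participation" and for the secondary outcomes. On adjustment it says: "Variables previously identified in the literature as relevant covariates (i.e. age and function as measured by baseline WST-C) will be controlled for". The list is introduced with 'i.e.', so it reads as complete, and site is not on it. Site comes later and in a different role: "Additional post-hoc sub-analyses will investigate the impact of site (using 2-way ANOVA"), with the remark that the study is powered for the primary analysis only.

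The Study Sites section also treats site analysis as post hoc, although it says: "The three study sites offer varied provincial approaches to MWC procurement as well as differences in geography, culture and climate", and adds provincial COVID-19 guidance to those differences.

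**The concern.** Balancing the arms within each site removes differences between sites from the true sampling variance of the treatment contrast. The analysis is credited with that gain only if the model contains site. Without it, any site variation stays in the residual. The reported standard error is then larger than the true one, confidence intervals are too wide, and the test rejects less often than its nominal 5%.

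This is not simply detail left to a later analysis plan. The protocol closes the covariate list and gives its only stratification factor a post-hoc role. An analyst following it would omit site. With 54 participants planned, the precision is worth having, provided site is in fact related to the outcome analysed.

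**Working it through.** **1. The plan's own figure.** Inputs from the Sample Size paragraph: f = 0.45, correlation 0.6, alpha 0.05, 90% power, between-factors repeated-measures ANOVA, N = 42, 20% attrition, 54 enrolled. With two groups and m measurements, the noncentrality is λ = f²·N·m / (1 + (m−1)ρ), on 1 and N−2 degrees of freedom.
- m = 2: λ = 0.2025 × 42 × 2 / 1.6 = 10.63, power 88.9%; 90% needs N = 44.
- m = 3: λ = 0.2025 × 42 × 3 / 2.2 = 11.60, power 91.4%; N = 40 gives 89.9%, so N = 42.
- Attrition: 42 / 0.8 = 52.5, so 53, and 54 gives 18 per site.

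The stated 42 is therefore reproduced with three measurements and nearly so with two. The sample-size paragraph mentions no site term.

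**2. Setting for the check.** N = 42 completers, three sites, 7 per arm per site, total residual variance fixed at 1. The effect implied by the plan's inputs is d = 2f / √((1+ρ)/2) = 0.90 / √0.8 = 1.006. Let s be the share of residual variance that lies between sites. The protocol does not give s. The values 0 to 0.20 are assumptions.

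**3. Standard error.** The true variance of the treatment difference is 4(1−s)/N, so its SD is 0.3086·√(1−s). Without site, the expected residual sum of squares is 40(1−s) + 42s = 40 + 2s on 40 df, a mean square of 1 + s/20. The reported SE is too wide by the factor √((1 + s/20)/(1−s)):
- s = 0.05: √(1.0025/0.95) = 1.027
- s = 0.10: √(1.005/0.90) = 1.057
- s = 0.20: √(1.01/0.80) = 1.124

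**4. Type I error and power.** With site in the model, the test is F on 1 and 38 df with λ = 10.63/(1−s). Without site, the numerator has the same λ, but the denominator is a noncentral chi-square on 40 df with noncentrality 42s/(1−s). Numerical integration gives the first figure in each cell. The figure in brackets comes from 20,000 simulated trials per setting.

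| Assumed s | Type I, no site | Type I, with site | Power, no site | Power, with site | Loss (points) |
|---|---|---|---|---|---|
| 0 | 5.0% (5.0) | 5.0% (5.2) | 88.9% (88.4) | 88.8% (88.4) | about 0 |
| 0.05 | 4.4% (4.4) | 5.0% (4.9) | 89.4% (89.6) | 90.3% (90.5) | 0.9 |
| 0.10 | 3.9% (4.0) | 5.0% (5.0) | 90.0% (89.8) | 91.8% (91.6) | 1.8 |
| 0.20 | 2.8% (3.1) | 5.0% (5.2) | 91.1% (91.2) | 94.4% (94.6) | 3.3 |

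At s = 0 the two degrees of freedom spent on site cost about 0.1 power point. Unadjusted power does not fall as s rises. It simply gains less than adjusted power does.

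**The case against.** Several points on the other side have force.

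- **The effect is conditional.** It needs site to predict the outcome after age and baseline WST-C. The protocol gives no figure for this, and at s = 0 nothing is lost. This stands.
- **The analysed quantity is change.** Stable site differences in level, such as those from procurement or geography, largely cancel within a person. Only site differences in change remain, for instance if restrictions or weather shift differently between baseline and week 7. Shares of 10% to 20% may therefore be too high for the primary outcome. This stands.
- **Perfect balance was assumed.** With 42 of 54 retained at random rather than exactly 7 per cell, a simulation put the type I error without site at 3.8% for a 10% share and 3.4% for a 20% share. The effect is slightly weaker but in the same direction.
- **The error is on the cautious side, and the stated aim of stratifying was comparable group size, not precision.** Both are true, but neither is a reason to leave the factor out of the model.
- **The covariate sentence concerns variables taken from the literature, so a design factor could still be added.** That would be more persuasive if the next paragraph did not assign site to post-hoc work.

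A reader might also infer more than the documents support:

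- **That the trial falls short of 90% power.** If d = 1.0 is taken in within-site SD units and site variance is added on top, power without site is about 86% at a 10% share and 83% at a 20% share. The protocol does not define its effect size that way, so those figures are not a shortfall against plan.
- **That actigraphy suffers most because of climate.** No calculation supports this. Recruitment is planned over about 12 months, so season also varies within site, and a site term would not capture that.
- **That language is a stated site difference.** The Study Sites section does not list it.

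**Conclusion.** The point holds as a modest, conditional matter of efficiency. The plan stratifies by site, omits site from the between-group model, and gives some reason to think that sites differ. If site explains 5% to 20% of the residual variance of change, standard errors are about 3% to 12% too wide, the actual type I error is about 4.4% down to 3%, and power is about 1 to 3 points below the site-adjusted analysis. These shares are assumptions, and at zero there is no material difference. The results also assume balanced completers and fixed total variance. The documents do not support reading this as bias, as an inflated false-positive rate, or as evidence that the planned 90% power is missed. The case for changing the model is that the gain, though small and uncertain, costs almost nothing.

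**What to change.** In the Data Analysis paragraph, add site (three levels, fixed effect) to the primary and secondary between-group models alongside age and baseline WST-C. Keep the treatment-by-site analysis as exploratory. Make the change before outcome data are analysed, so that including site is not itself a post-hoc choice.

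The cost is one phrase and 2 degrees of freedom. It needs no new data and no change to the sample size.

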**Assessments.** Our experience in the feasibility studies, confirmed the pragmatic and financial challenges of attending appointments for individuals with a mobility limitation, as reported in the literature. A Research Assistant at each site will administer the outcome measures at baseline and subsequent data collection points; participants will receive a stipend of \$50. Due to the ongoing coronavirus pandemic and in line with the ever-changing guidelines and regulations, participants will be offered a variety of options for stipend payment as well as for data collection. For payment, participants will be provided with the following options:

- 1) A Visa or MasterCard gift card sent via postal mail or delivered to the participant's address (participant name and information would remain confidential);
- 2) A cheque sent directly to the participant's financial institution for deposit (the participant would agree to providing their name and financial institution address to the UM Finance Department);

For data collection, the questionnaires will always be provided to participants in advance by email, non-contact drop off, and/or post. Participants will be provided the following options for questionnaire completion:

- 1) The participant completes the questionnaires (except the WhOM) independently and returns them either electronically (i.e., email or text the form or image of the form) or in a self-addressed stamped envelope (SASE) by post. The RA will conduct a follow-up phone call or videoconference to confirm or correct any missing data and administer the WhOM.
- 2) The participant (i.e., those with internet access) completes the questionnaires (except the WhOM) online using the secure Qualtrics platform (i.e., PHIA/FIPPA compliant and HREB acceptable from personal communication). Participants receive a web link and ID

number to ensure confidentiality. The RA will conduct a follow-up phone call or videoconference to confirm or correct any missing data and administer the WhOM.

- 3) The RA will administer and score all of the questionnaires over the phone.
- 4) The RA will administer and score all of the questionnaires via teleconference using the Zoom or MS Teams platform configured for research purposes (i.e., PHIA/FIPPA compliant). The RA will “screen share” the questionnaires (either in original form or using the Qualtrics platform) and document the participant’s responses.

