uses user-specific activities, addressing potential sex and gender differences in viewing participation. Two published literature reviews identify the WhOM as the most client-centred and psychometrically robust tool among participation outcomes for wheelchair users. The WhOM is administered as a semi-structured interview. Respondents identify 10 activities (5 performed inside and 5 performed outside of the home), rating their satisfaction with performance on an 11-point scale (0-10) for each activity. The RA will complete the WhOM with the participant via telephone or Zoom/MS Teams teleconference. The participant will be provided with the WhOM form along with the other questionnaires in advance, via post or email. The RA will collect the data by telephone or teleconference and (subsequently) enter it into the MS Teams database. The WhOM demonstrates good reliability (Test-retest ICC = 0.83-0.88; Inter-rater ICC = 0.90-0.91) and validity (correlations with LIFE-H:  $r_s = 0.3-0.5$ ) in use among individuals with spinal cord injury and older adults (Test-retest ICC = 0.77–1.00; correlation with QUEST  $r_s = 0.36 - 0.45$ ). (Auger et al., 2010) A change of 1.6 points has been identified as clinically meaningful. Combined results from our feasibility studies found a large effect size ( $d = 0.93$ ; 95%CI 0.54, 1.33), with mean improvement of 2.3 points. WhOM activities identified by participants (but not the scores) will be shared with their peer trainer to facilitate tailoring of the TEAM Wheels program.

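### Outcome collection is labelled blinded, but as written the staff role that holds the allocation also conducts the primary outcome interview, and the 6-month assessment covers one arm only

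*Protocol*

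**What the plan says.** **The label.** The protocol's Methods section uses the word blinded twice for outcome collection. On the timing of the first peer session it says that "for control group assignments this will be scheduled after blinded post-treatment data collection is complete". On retention it says: "The Research Assistant will also arrange blinded follow-up (retention) data collection for treatment group participants 6 months after post-treatment data collection".

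**Who learns the allocation.** After baseline data are entered, "The site Research Assistant (RA) will then obtain the participant’s group assignment". This sentence defines the abbreviation RA.

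**Who collects the outcomes.** The Methods text on data handling says: "Data collection for all time periods (baseline, post-treatment, and 6-month follow-up) will be completed by the RA". The Assessments paragraph adds: "A Research Assistant at each site will administer the outcome measures at baseline and subsequent data collection points". For the primary outcome, the Outcome measures section says: "The RA will complete the WhOM with the participant via telephone or Zoom/MS Teams teleconference".

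**What else the RA does.** Under Treatment Group, the RA arranges Session 1, configures the tablet and hotspot, sends or delivers the equipment, and helps with set-up and troubleshooting. Under Control Group: "The site Research Assistant will make contact with control group participants at the end of weeks 2 and 4". The week-4 contact is also used to book the week-7 assessment.

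**The concern.** The WhOM is a semi-structured interview. The participant names activities and rates satisfaction with each from 0 to 10, and the RA elicits and records the answers. An interviewer who knows the arm can influence a rating through prompting, probing or tone without intending to. The word blinded tells a reader that this route is closed. If the person interviewing at week 7 has shipped a tablet to one participant and made waiting-list calls to another, it is open, and a report that follows the protocol's wording would claim a protection that the trial did not have. The outcome affected is the primary one.

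**Working it through.** **Step 1. Trace the tasks given to the RA.**

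| Task | Where in the protocol | Does it reveal the arm? |
|---|---|---|
| Obtains the group assignment after baseline | Methods | Yes |
| Schedules the first peer session by arm | Methods | Yes |
| Arranges Session 1; configures, delivers and supports the tablet | Treatment Group | Yes: before post-treatment collection, only treated participants receive it |
| Contacts controls at weeks 2 and 4 and books week 7 | Control Group | Yes: controls only |
| Completes data collection at all time points | Methods | This is the outcome assessment |
| Administers the WhOM | Assessments; Outcome measures | This is the primary outcome |

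Assessments gives four ways to complete the questionnaires. The first two allow self-completion but exclude the WhOM, which the RA then administers by phone or video. In the other two the RA administers everything. The RA therefore conducts the WhOM interview in all four.

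**Step 2. Look for a masking procedure.** The one measure described is the undisclosed block size. It makes upcoming allocations hard to predict. It does not keep an assessor unaware of an allocation already made. No separate assessor is named.

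**Step 3. The 6-month visit.** Follow-up data are collected from the treatment group only. Being assessed at 6 months identifies the arm, whoever conducts the interview.

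**Step 4. Illustration of sensitivity (post-treatment, between groups only).** The contradiction above does not depend on this step.

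*The protocol's own sample size, for context.* Inputs: f = 0.45, correlation 0.6, alpha 0.05, power 90%. For a between-factors repeated-measures ANOVA, λ = f²·N·m/(1 + (m − 1)·ρ) with 1 and N − 2 degrees of freedom. The number of measurements m is not stated.
- m = 2, N = 42: λ = 0.2025 × 42 × 2/1.6 = 10.63, power 0.889.
- m = 3, N = 42: λ = 0.2025 × 42 × 3/2.2 = 11.60, power 0.914.

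The stated 42 is reproduced within rounding, and 42/0.8 = 52.5 leads to 54 with equal arms and sites. Nothing here needs to change.

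*Assumed inputs for the illustration.*
- SD = 2.3/0.93 = 2.47 points. This assumes that the feasibility mean improvement and d can be combined in this way; the protocol does not say how d was standardised.
- Baseline-adjusted comparison with correlation 0.6, so the residual variance is 1 − 0.36 = 0.64 SD².
- Assumed interviewer bias b of 0.3 or 0.6 points. Neither value has a source in the protocol.

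SE = √(0.64 × 4/N) in SD units. With x = b/SE, the rejection rate under no true effect is 1 − Φ(1.96 − x) + Φ(−1.96 − x).

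| N analysed | SE (SD) | SE (points) | b = 0 | b = 0.3 | b = 0.6 |
|---|---|---|---|---|---|
| 42 | 0.247 | 0.61 | 5% | 7.8% | 16.6% |
| 54 | 0.218 | 0.54 | 5% | 8.6% | 20.0% |

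Both assumed biases are well below the 1.6-point change that the protocol calls clinically meaningful.

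**The case against.** **A second, blinded RA may be intended.** The number of RAs per site is never stated. The Research Assistant is said to arrange the blinded follow-up, which is not the same as conducting it, and Assessments speaks of a Research Assistant at each site without saying that this is the person who handles allocation. This stands in part. A reader might infer that one person per site is established to know every participant's arm. That is the natural reading, because RA is defined once and all data collection is given to the RA, but the protocol does not say it outright. The text between the Sample Size and Study Sites headings was also not available for this check. If a second assessor is intended, the protocol still has to say so.

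**The scores are the participant's own.** This stands. The RA elicits and records ratings and does not judge performance, so scoring discretion is small, and the protocol cites inter-rater ICCs of 0.90 to 0.91. Prompting remains possible in a semi-structured interview.

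**Participants know their arm anyway.** This also stands. A reader might infer that a blinded interviewer would make the primary outcome free of knowledge of allocation. It would not: it removes interviewer influence and leaves participant expectation untouched.

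**The percentages prove nothing.** Agreed. Any rejection rate follows from the bias that is put in. A reader might take 8% or 17% as an estimate of the trial's actual error rate; the protocol supports no such estimate. The figures do not apply at 6 months either, where the analysis is within the treated arm.

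**Conclusion.** The protocol claims a property that its own procedures do not deliver. As written, the post-treatment WhOM interview is not blinded, because the only RA role defined both holds the allocation and conducts the interview. This rests on reading RA as one role throughout and on the absence of any described masking procedure in the text examined. The 6-month label is wrong on any reading.

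The documents support neither a finding that bias has occurred nor a figure for its size. What is at stake is what the trial may claim about its primary outcome: an interviewer-blinded assessment, or a participant-rated outcome collected by an unblinded interviewer.

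**What to change.** 1. **6 months:** delete blinded. This is a wording change only.
2. **Post-treatment:** choose one.
   - *Keep the claim and support it.* State that the WhOM is administered by existing staff with no access to allocation and no part in the intervention logistics or control contacts, and that participants are asked not to reveal their group. Interviews are already by phone or video, so no travel is added. If the assessor is an RA from another site, the Methods statement that personal information is not shared among the research teams must be amended, the consent wording changed, and French-language coverage confirmed for Quebec City. The assessor would need contact details and, presumably, the participant's baseline WhOM activities.
   - *Drop the claim.* Delete blinded, and report the WhOM as a participant-rated outcome collected by an unblinded interviewer. This is a wording change only.
3. **In either case:** state that participants know their arm, so a blinded interviewer would remove interviewer influence only.
4. **Reconcile** Methods, Assessments, Outcome measures, Treatment Group and Control Group so that each RA task is assigned to a named role.

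Having participants write their WhOM ratings beforehand is not a wording-only alternative. Assessments excludes the WhOM from self-completion and Outcome measures specifies an interview, so it would change how the primary outcome is administered.
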